#### Secondary outcomes and data collection methods

Secondary outcomes will include the following variables associated with mobility behaviours: kilometres travelled by active and sustainable mobility, and the modal share of active mobility, physical activity measured by the Sensedoc™ 2.0 sensor and the IPAQ (i.e., International Physical Activity Questionnaire, [60]), exposure to air pollution (i.e., concentration of fine particles PM_2.5_ and oxidative potential) measured by an air pollution sensor (MicroPem™), activity programme measured by the mobility logbook and, quality of life measured by a survey [61] (see Fig. 5).

#### Mediators, moderators, and collection methods

We will investigate whether the effects of the intervention on mobility-related outcomes are mediated by several psychological constructs, including notably attitudes and self-efficacy towards the car [66], active mobility habits [65], motivational stages of mobility change [62] (see Table 1 for all the details), which will be collected by online surveys, using the platform Sphinx iQ2 v 7.3.1.0 (this platform is located at the university to ensure that the data remain in Europe as required by the European data protection law). Self-control constructs, including subjective vitality [70], temptation, conflict, and resistance [71], will be measured on a daily basis during the data collection weeks, through online surveys on the platform Sphinx iQ2 v 7.3.1.0 as well.

We will also investigate if the efficacy of the intervention depends on several socio-demographic and geographic variables, including the number of children, number of cars, trip chaining, mobility biographies [77], cyclability and density of home address and destination address. They will be measured through the data collected by the online surveys, on the platform Sphinx iQ2 v 7.3.1.0.

#### Reach and quality of the implementation

The reach of the intervention (i.e., the number of people contacted by the implementation team, the number of eligible participants, and the enrolled participants) will be assessed by collecting the data from the first contact to the enrolment of participants. Finally, the quality of the implementation will be assessed by analysing a document filled up by the programme implementer at every appointment related to the intervention (i.e., a checklist for every task to be done during the S0+ and S1 appointments).

### Data management and statistical methods

#### Data quality, management, storage, access and confidentiality

In order to monitor the quality of the data, one member of the implementation team and few members of the scientific team checks the correct completion of logbooks, online questionnaires, and the presence of missing data collected by the sensors.

Data from the sensors (Sensedoc™ and MicroPem™) are downloaded after each session to an encrypted computer and stored on a secure and back-up online storage. Data from the online surveys are downloaded twice a month on the same computer. Furthermore, data from all devices (contact forms, sensors, mobility logbooks and online surveys) will be structured and saved in two different blocks stored on distinct servers:

Block 1 will contain the contact file with the names, addresses and contact details of participants for setting the appointments and sending/recovering material. This file will be in the management tool, encrypted and kept separate from other data by the implementation team coordinator. The correspondence table between the code of the participants and their name will also remain in the management tool, a software as a service (SaaS) deployed on a specific server of the university infrastructure accessible only by the implementation team.

Block 2 will contain all the collected data from surveys and sensors. They will be stored locally, on the secured data centre of the university, with access restricted only to InterMob faculty members and implementation team, in line with data protection law. The raw data will be stored by the programme implementers. The data from the GPS/accelerometer and pollution sensors will be downloaded at each return from the field. The survey data, coming from the Sphinx platform, will be regularly uploaded to the storage space. Only implementation team and informatician administrators will have read/write access. The scientific team will only have read access to raw data. Moreover, they have folders with data pre-processing and processing with read/write access, not accessible to the implementation team. Finally, another folder will be created for sharing with external partners.

#### Data monitoring, harms and auditing

No data monitoring committee has been set up for this study because there is no strong suspicion that the interventions can potentially harm the participants. Nevertheless, there is a risk that some travel modes (e.g., cycling) might lead to traffic accidents. For this reason and in order to protect the participants as much as possible, the helmets will be mandatory throughout the study. At the psychological level, some participants may experience guilt if they do not manage to reduce car use. In order to limit this risk, the team responsible for the implementation insists on a non-guilty and valorising communication and coaching during their face-to-face meetings with the participants (i.e., motivational interviewing). Moreover, participants will be encouraged to share with the implementation team any adverse events associated to mobility change. This information will be stored in a specific document by the coordinator of the implementation of the study.

The coordinator of the implementation of the study and the coordinators of the project have one meeting per week to audit the trial conduct.

#### Ancillary and post-trial care

No ancillary and post-trial care will be provided.

#### Statistical methods

##### Analysing the effects of the intervention on primary and secondary outcomes by using multilevel modelling

The analysis of the effectiveness of the intervention on the primary outcome (reduction of car use, see "Primary ouctome and data collection methods") and secondary outcomes (mobility-related variables described in the section "Secondary outcomes and data collection methods") will be examined at the very short term (3 months after the start of the intervention: S2), the short term (7 months after the start of the intervention: S3), the medium term (1 year after the start of the intervention: S5) and the long term (18 months after the start of the intervention: S6). More precisely, we will test the differences in car use reduction between the experimental arm and the active control arm, by using multilevel modelling, which is appropriate when data are nested, as it is the case here with several measurement times per participant (e.g., [78]). Moreover, multilevel modelling offers the possibility to analyse incomplete data sets, which is particularly relevant given the duration of the study, which makes likely the occurrence of missing data [79]. For this purpose, we will follow the steps recommended by [80]:Prepare the data by differentiating between- and within-individual constructs.Centre the within-individual variables by participant (i.e., “group centring”).Create a first “constraint” model (a model containing all the random and fixed variables of the final model) and a “null” model including only the “intercept” equal to 1 and only one random variable associated with the identity of the participant (i.e., 1 | Id) to check the intraclass correlation coefficients (ICC).Build the main model.Evaluate the normal distribution of residuals, Cooks distance and influential cases.

The main model will include the following fixed effects: arm, time, and arm x time interaction, with random intercepts for participants and random linear slopes for repeated measures at the participant level.

Moreover, the statistical analysis will follow intention-to-treat principles. This means that once a participant has been randomly assigned to an arm (i.e., experimental or control), his/her data will be included in the analysis [81]. More precisely, even if a participant has not adhered to the intervention or has not finished the study, his/her data will be included to all the analysis.

In addition, we will carry attrition analysis by comparing the characteristics of the participants that drop out the study and the participants that completed the study (e.g., compliance with eligibility criteria, sociodemographic and geographical characteristics).

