### Participant timeline

#### Recruitment, allocation, and blinding

The participants will be recruited through different sources: mailing lists from former studies conducted by the research team (QAMECS-SHS and EMC^2^ 2019–2020, local travel surveys, surveys from other laboratories and projects), publicity in local events related to transport or environment, publicity in community newspapers, interventions with the mobility referents of companies in the Grenoble region and, social networks (e.g., Facebook, LinkedIn and Instagram). The people that will be interested to participate in the InterMob study will fill up an online form in order to be contacted by a member of the implementation team (the information in this form includes the first name, a telephone number, an email address, municipality of residence, sex, age, educational attainment and the availability for receiving a phone call). The implementation team will call interested people to explain the study procedure and to administer the eligibility questionnaire. A few days later, the implementation team will call again the eligible people to ask if they accept to participate in the study. If a participant accepts, she/he will be randomly allocated to the experimental or active control arm. For this allocation, a randomisation list for the whole study was created by blocks of six before the beginning of the enrolment (i.e., it exists three possibilities to be in the experimental arm and three possibilities to be in the active control arm) by a member of the scientific team. The list was implemented in the management tool software developed by the team with WebDev for the study. The management tool automatically assigns each eligible participant to a group (the n-th participant is assigned to the group corresponding to the n-th position of the list).

Concerning blinding, the implementation team (programme implementers) will not be aware of group allocation at baseline (S0), but blinding will be impossible afterward, as the programme implementers deliver different contents to each arm through face-to-face interviews with participants. The researchers will not be aware of group allocation at any time, and the researchers responsible for analysing the data will be blinded to the treatment allocation. Double blinding will not be possible given that allocation concealment is impossible for participants in such an intervention.

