#### Timeline of the study

Participants enrolled in the study will have a first two hours with a programme implementer (“Session 0” or S0, see Fig. 4). At the beginning of this meeting, the participant reads and signs an informed consent form (cf. Supplementary materials). She/he fills up a first questionnaire assessing her/his quality of life, biometrics, mobility behaviours, the weekly duration of moderate-to-vigorous physical activity, socio-demographic information and psychological constructs 1, 2 and 3, as well as a mobility logbook assessing her/his last week mobility (for more details about the tools and surveys, see Table 1). Then, the implementation team explains how to correctly carry the Sensedoc™ and MicroPem™ sensors (see Fig. 5), and the participant is instructed to start carrying them from the next 7 days. At the end of the session, the sensors are collected by the programme implementer. Moreover, during this session, the participants receive a daily survey on their telephones measuring psychological constructs 4. Two weeks after S0, the participants have the first intervention appointment (S0+) that will be described in the intervention subsection.

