#### Power analysis and sample size

Sample size is difficult to estimate when using multilevel modelling as in the present study, given that sample size calculation is sensitive to the values of all the fixed and random parameters included in the models. As such, we estimated the sample size based on the expected effect size of the intervention at the end of the intervention only, which was an expected difference of 17% of the trips made by car at the end of the intervention [72] between the experimental and the control group. With a significance level of 0.05 and a statistical power of 80%, the a priori power analysis conducted with G*Power 3.1.9.4 [73, 74] indicated that 150 participants per arm (a total of 300 participants) are necessary for finding a difference of 17% between the experimental and the control arms at the end of the intervention. We will therefore recruit participants until exhaustion of our financial and human resources, with this ideal target of 150 participants per arm. Once recruitment is finished, we will compute the minimal statistically detectable effect that can be observed based on the final number of participants [75].

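### The main model uses no baseline adjustment; a common S0 mean or an S0 covariate would generally give more precise session contrasts from data already collected

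*Protocol article*

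**What the plan says.** The first subsection under Statistical methods, on multilevel modelling of the primary and secondary outcomes, says that "The main model will include the following fixed effects: arm, time, and arm x time interaction". It states the aim as "we will test the differences in car use reduction between the experimental arm and the active control arm" and names four sessions of interest: S2, S3, S5 and S6. The random part of the model is specified as one "with random intercepts for participants and random linear slopes for repeated measures at the participant level". The subsection names no baseline covariate and no common-baseline constraint. It does not say whether fixed time is categorical or linear, or whether S0 is one of the outcome rows.

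Table 1 shows car use measured at S0 and at every later session. On sequence, the section on recruitment, allocation and blinding says "If a participant accepts, she/he will be randomly allocated to the experimental or active control arm", which places allocation before the S0 visit. The implementation team "will not be aware of group allocation at baseline (S0". The Timeline section adds "Two weeks after S0, the participants have the first intervention appointment (S0", so intervention content starts only at the S0+ visit. Allocation is in blocks of six, and no stratification by baseline car use is described.

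**The concern.** An effect stated as a difference in reduction needs a reference point, and S0 is the only session before the intervention. There are two natural readings:

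- S0 is a level of categorical time. A free arm effect plus arm x time then makes the contrast at each session the between-arm difference in mean change from S0. With complete data this is exact, whatever the covariance structure.
- The outcome is itself change from S0. The contrast is then a change score by construction.

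On both readings the S0 means are estimated separately by arm and then subtracted in full. If the arms can be taken to have equal expected car use at S0, this gives up information. What is at stake is the width of the confidence intervals for outcomes measured both at S0 and at follow-up. It matters because the section on power and sample size treats 300 participants as an ideal target, with recruitment limited by resources.

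**Working it through.** **Inputs.** The model, session schedule and allocation sequence are as stated in the article. The baseline-to-follow-up correlation rho, and the ratio k = SD(S0)/SD(follow-up), are not given; values below are assumptions. The article has no figure of its own for this point. Its 150 per arm is for the end-of-intervention comparison only and cannot be rederived, because no control rate or SD is given; it is not needed here.

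**Step 1: one follow-up, equal variances (k = 1).** Per-participant variance in units of the follow-up variance:

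- change score: 2(1 − rho)
- baseline-adjusted or common baseline: 1 − rho²
- fraction removed: 1 − (1 + rho)/2 = (1 − rho)/2
- equivalent increase in sample size: 2/(1 + rho) − 1

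| rho (assumed) | change score | adjusted | variance removed | equivalent extra sample |
|---|---|---|---|---|
| 0.3 | 1.40 | 0.91 | 35% | 54% |
| 0.5 | 1.00 | 0.75 | 25% | 33% |
| 0.7 | 0.60 | 0.51 | 15% | 18% |
| 0.8 | 0.40 | 0.36 | 10% | 11% |

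At rho = 0.9 the fraction removed is 5%.

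**Step 2: in terms of power.** Suppose a comparison of follow-up values alone has 80% power at two-sided 0.05 (the article gives the level and power but not the sidedness). With relative variance v, power is Φ((1.960 + 0.842)/√v − 1.960). Change score against common baseline then gives 66% against 84% at rho 0.3, 80% against 90% at 0.5, and 95% against 97.5% at 0.7. Below rho = 0.5 the change score is weaker than the follow-up-only comparison.

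**Step 3: unequal variances.** The fraction removed becomes (k − rho)²/(1 + k² − 2·rho·k). For example, k = 0.8 and rho = 0.5 give 0.09/0.84 = 11%.

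| k (assumed) | rho 0.3 | rho 0.5 | rho 0.7 | rho 0.8 |
|---|---|---|---|---|
| 1.0 | 35% | 25% | 15% | 10% |
| 0.8 | 22% | 11% | 2% | 0% |
| 0.7 | 15% | 5% | 0% | 3% |

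The gain is zero when k = rho and is never negative.

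**Step 4: the stated random structure.** Generalised least squares was run with 150 per arm, complete data on all eight sessions, and random intercepts and linear slopes. The assumed ICC ran from 0.3 to 0.8, with several assumed slope variances and an intercept-slope correlation of 0 or −0.3. Dropping the arm effect at S0 removed 4% to 38% of the variance at S2, S3, S5 and S6 with categorical time. With linear time, where the effect is a slope difference, it removed 1% to 28%.

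**Step 5: if allocation did affect S0 (k = 1).** Suppose S0 in one arm is shifted by d.

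- Shift at S0 only: the change score is off by d, the adjusted contrast by rho·d.
- Shift also present at follow-up (for example, different people attending S0): the change score is off by d − d = 0, the adjusted contrast by d − rho·d = (1 − rho)d.

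Neither analysis is uniformly safer.

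**The case against.** The strongest reply is that nothing here is an error. Arm, time and arm x time is a standard model. Under randomisation it is unbiased with a valid type I error, and its standard error already reflects chance imbalance at S0. An article may also leave baseline adjustment to a fuller plan. The first part stands in full. The second carries less weight, because the article lists the fixed effects, so a later plan would have to alter that list to add an adjustment.

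Three stronger readings are tempting, and the documents do not support them:

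- A reader might infer that the effect is definitely a change score. S0 as an outcome row and categorical time are inferences. The four named sessions favour session-specific contrasts, but the random linear slopes leave linear time open. With missing data the estimate is not a plain change score either.
- A reader might take 10% to 35% as this trial's loss. It follows from an assumed rho and equal SDs. Entry is restricted to people who mainly use a car or motorbike on weekdays, which may compress S0 modal share. S5, one of the named sessions, has no sensor, whereas S0 has both sensor and logbook. Equal SDs are therefore not established.
- A reader might say that randomisation guarantees equal S0 means. Participants are allocated on acceptance by telephone, before they sign consent and are measured at S0. Implementers are unaware of the arm then, but the article does not say whether participants are. S0 includes a self-reported logbook, and attendance could differ by arm. Step 5 shows that a failure of the assumption can bias the adjusted contrast.

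**Conclusion.** The point holds as an efficiency improvement, not as a flaw in validity. On the two natural readings, the planned contrast is an unadjusted difference in change from S0, and baseline adjustment would generally be more precise. The size depends on quantities the article does not give. It is 35% to 10% of the variance for an assumed rho of 0.3 to 0.8 with one follow-up and equal SDs. It is less in the cases tried with S0 less variable than follow-up, down to nothing when the SD ratio equals rho. It is about 1% to 28% with linear time over all eight sessions.

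The common S0 mean is reasonable because intervention content starts two weeks later and implementers do not know the arm at S0, but it remains an assumption. The point does not reach every listed secondary outcome: Table 1 includes items measured only at S0 (accessibility, cyclability) and items never measured there (reach, implementation quality).

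**What to change.** State that fixed time is categorical and how S0 enters the model. Then choose one of two forms, for outcomes measured both at S0 and at follow-up:

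- keep S0 as an outcome row and fit session plus arm x post-baseline-session terms, with no arm effect at S0; or
- model S1 to S7, or those of them at which the outcome is measured, with the S0 value as a covariate.

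State the common-baseline assumption openly, say whether participants know their arm when S0 is measured, and report S0 attendance and S0 means by arm. The model as now planned can be kept as a sensitivity analysis. If a gain is quoted, label rho and the SD ratio as assumptions.

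The cost is a short change to the model specification, made before any unblinded analysis, and the added assumption about S0. No new data are needed.

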##### Analysis of the mediatiors of the effects of the intervention

To analyse the mechanisms explaining potential effects of the intervention on car use reduction and mobility-related variables, the investigators will use multilevel mediation models to test the mediating role of psychological constructs (e.g., intention toward active and sustainable mobility, active mobility habits, self-efficacy towards active mobility) in the intervention mobility-related variables relationships.

##### Analysis of the moderators of the effects of the intervention

To analyse the possible moderators of the effects of the intervention on car use reduction and mobility-related variables, the investigators will assess in multilevel models the statistical interactions between socio-demographic, geographic and psychological variables (e.g., number of children, travelled distances, accessibility of home and work, self-control variables) and the allocation to the experimental or control arm. This will allow identifying to what extent geographical, socio-demographic, and psychological variables moderate the effects of the intervention on car use reduction and mobility-related variables.

## Discussion

InterMob study is a 24-month randomised controlled trial aiming to reduce car use of car and motorbike regular drivers. For this purpose, InterMob will include a two-arm intervention of 6 months: an experimental arm that combines the use of behaviour change techniques previously identified as being successful at changing mobility behaviour (e.g., personalised transport advice, goal setting, action planning) and free access to public transport or/and to a bike; and an active control arm which will target raising awareness about the consequences of air pollution and the link between air pollution and car use.

InterMob will aim to address the limitations of prior behaviour change interventions in the field, including lack of theory-based intervention elaboration, long-term follow-ups, high-quality methodologies (e.g., randomised controlled trial), and in situ measures [28, 58, 82–84]. By addressing these limitations, InterMob will allow deepening our knowledge of the long-term effects of a theory-based intervention tested in a 2-arm randomised controlled trial that combines *hard* and *soft* levers, with use of in situ measures of mobility and correlates.

Furthermore, we will aim to understand the psychological mechanisms that explain the potential effects of the proposed intervention on mobility, as well as the moderating role of geographical, socio-demographic, and psychological factors in this relationship, to better understand the conditions under which the intervention is effective.

Finally, InterMob study will measure the effects of the intervention not only on mobility change, but also on health-related outcomes such as physical activity and exposure to air pollution. Therefore, the results of our study might imply supplementary arguments for governments and politicians to promote car reduction and active and sustainable mobility, and deepen what has been modelled in past studies [85].

